### Sample size calculation

The power calculation is based on a constrained longitudinal data analysis (cLDA) model (17, 18) and calculated using an approach presented by Stroup (19). To have at least 90% power to detect a difference of 2.7 ml/kg/min in pVO2 after 12 months, 90 subjects per group (180 in total) are required based on a two-sided test and setting alpha equal to 0.05. The effect size of 2.7 is a weighted average of the expected effects in the three stages i.e., 0.20 × 1 ml/kg/min (Stage C) (20, 21) +0.30 × 2.5 ml/kg/min (Stage B) +0.50 × 3.5 ml/kg/min (Stage A) (22, 23). A common standard deviation of 5, a correlation between baseline and 12 months equal to 0.50 and a drop-out rate at 12 months as high as 40% were assumed (24). However, the sample size will be increased to 312 patients in total (156 per group) such that for two key secondary outcomes standardized effect sizes as small as 0.45 and 0.40 can be detected with more than 90% and 80% power, respectively (using a cLDA model assuming—as for the primary outcome—a baseline-year correlation of 0.50% and 40% dropout at 12 months). For example, for the key secondary outcome (moderate to vigorous physical activity, MVPA) a standardized mean difference equal to 0.42 corresponds to a difference of 1,235 steps (25). Note that for the power calculation of the key-secondary outcomes an alpha-level of 0.05/2 = 0.025 was used.

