#### Outcome measures and data collection

Assessments will be performed at baseline before randomization (T0), at 4 months (T1) as this is the median intervention duration in most supervised exercise studies, at the end of the 1-year intervention (T2) and after two years of FU (T3). The main goal is to assess the effectiveness of the intervention on different biopsychosocial outcomes at 1- and 2-year FU. A tabulated overview of the primary, secondary and other outcomes measured at the different time points is provided in Table 3.

**Table 3 T3:** Tabulated summary of trial schedule.

Outcomes	Instrument	T0	T1	T2	T3
Primary outcome					
Exercise capacity	Peak oxygen uptake via cardiopulmonary exercise test on cycle ergometer	X	X	X	X
Secondary outcomes					
Physical activity	ActiGraph GT9X Link	X	X	X	X
Health related physical fitness					
Body morphology/composition	Body mass (body weight scale), height (stadiometer)and waist circumference (stretch-resistant measuring tape). Bioelectrical impedance will be used to assess fat and fat-free mass.	X	X	X	X
Handgrip strength	Isometric handgrip grip strength of both hands using a Jamar Hydraulic Hand Dynamometer (Sammons Preston Inc.).	X	X	X	X
Quadriceps muscle strength	Three voluntary maximal isometric contractions (6 s) performed at a 60° angle of the knee, with a 60-second rest period between each test, on a dynamometer (Biodex Medical Systems Inc., 840–000 System 4, New York, USA).	X	X	X	X
Quadriceps muscle endurance	25 repetitive maximal isokinetic knee extensions at 180°/s, performed on a dynamometer. Mean torque and percentage decrement score will be used as markers for muscle endurance.	X	X	X	X
Cardiovascular health					
Blood sampling	Glucose homeostasis, blood lipid profile, NT-proBNP	X		X	X
Rest and stress echocardiography	Vivid E95 ultrasound scanner, semi-supine bicycle ergometer (Ergoline) is used for stress echocardiography.	X		X	X
Health related QoL & psychosocial wellbeing	EQ-5D-5l Questionnaire	X	X	X	X
	SF-36 Questionnaire	X	X	X	X
	Exercise Self-Efficacy Scale	X	X	X	X
	Exercise Barriers Questionnaire	X	X	X	X
	Social Support Questionnaire	X		X	X
Implementation potential	User experience Questionnaire			X	** **
	Adherence to exercise program			X	** **
	Patient Debriefs: Self-reported and objective measures (exercise log, heart rate measurements)			X	** **
Evaluation towards cost-effectiveness	Productivity Cost Questionnaire	X	X	X	X
	Medical Consumption Questionnaire	X	X	X	X

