	*Quality of life* via *EQ-5D-5l questionnaire*	X	X	X	X
Safety monitoring	Adverse events reporting by patients	X——————––X			
Other outcomes					
Sociodemographic characteristics	General Questionnaire	X	X	X	X
Substudy: muscle metabolism	Device for muscle oxygenation measurements (PortaMon)	X		X	
Substudy: vasoreactivity/vasomotor function	Flow mediated slowing via Vicorder	X		X	

T0, baseline; T1, measurement at 4 months; T2, measurements at 1 year; T3 measurements at 2 years; NIRS, near infrared spectroscopy; FMS, flow mediated slowing.

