#### Secondary outcome measures

##### Physical activity

A validated tri-axial accelerometer (ActiGraph™ GT9X Link, ActiGraph LLC, Pensacola, Florida, USA) will be used to objectively measure the patient’s physical activity level (30). Participants will be asked to wear the ActiGraph GT9X Link on the non-dominant wrist for 24 h/day for 7 days. Measurements will be considered valid when at least 3 weekdays and 1 weekend-day of 10 h wear-time have been recorded (31). ActiLife software will be used to extract the raw data from the physical activity monitor which will then be transferred to the physical activity core lab at KU Leuven for offline analysis. The following parameters will be determined: number of steps (key secondary outcome), energy expenditure (total and active), time spent doing MVPA (key secondary outcome) and number of sedentary bouts.

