### Statistical analysis

The full analysis set (FAS) will, in accordance with the intent-to-treat principle, include all randomised patients according to their randomised treatment. The FAS will be used for the evaluation of all efficacy and safety endpoints. Patients from the FAS with major protocol deviations will be excluded from the per protocol set (PPS). A cLDA (18) model will be used to compare the pVO2 at 12 months between both groups. In this model, both the baseline pVO2 and post-baseline pVO2 values (4 months and at 12 months) are modelled as dependent variables, as opposed to a longitudinal ANCOVA model in which the baseline value is included as a covariate. The comparison at 12 months will be based on a two-sided test, setting alpha equal to 0.05. An unstructured covariance matrix will be used for the three longitudinal measurements. The HFpEF stage will be added as a factor in the model and the differences between the groups are allowed to differ between the stadia. The intervention effect will be calculated as a weighted average of the stage-specific effects. The estimation of the model will be likelihood based and results are therefore valid under the MAR (missing at random) assumption, i.e., subjects with a missing pVO2 value at a specific timepoint are assumed to be well represented by other subjects not having a missing value at that timepoint and having the same observed values at the other timepoints. Note that the comparison at 4 months, which will be derived from the same model, is a secondary outcome. The cLDA model (restricted to baseline and 12 months) will also be used for the comparison of the two key secondary outcomes, applying a Bonferroni-Holm correction.

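### The key secondary model leaves out the scheduled 4-month activity measurement; including it is a free gain in precision and robustness to dropout, not a power correction

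*Protocol article*

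**What the plan says.** All references are to the protocol article.

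- **Key secondary model (Statistical analysis):** "The cLDA model (restricted to baseline and 12 months) will also be used for the comparison of the two key secondary outcomes". A Bonferroni-Holm correction applies across the two outcomes.
- **Primary model (same section):** for pVO2, "both the baseline pVO2 and post-baseline pVO2 values (4 months and at 12 months) are modelled as dependent variables", and "An unstructured covariance matrix will be used for the three longitudinal measurements".
- **Source of the key secondary outcomes (Physical activity):** the accelerometer yields "number of steps (key secondary outcome), energy expenditure (total and active), time spent doing MVPA (key secondary outcome").
- **Schedule (Table 3):** the row reads "ActiGraph GT9X Link X X X X", so all four visits are marked. The footnote defines "T1, measurement at 4 months; T2, measurements at 1 year".
- **Dropout (Sample size calculation):** for the primary outcome, "a drop-out rate at 12 months as high as 40% were assumed". The same 40%, and a baseline-to-12-month correlation of 0.50, are carried over to the key secondary outcomes.
- **Objectives (Secondary objectives of the trial):** steps and MVPA are to be compared at one and two years; pVO2 is also to be compared at 4 months.

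**The concern.** The section supports its likelihood-based analysis by assuming that a subject with a missing value resembles others who share the same observed values at the remaining visits. That sentence is written for pVO2, but the key secondary outcomes use the same model type and so rely on the same logic. Once month 4 is removed, the only remaining visit is baseline. Two patients with equal baseline activity, one still active at month 4 and one who had stopped, are then treated as interchangeable when one of them has no 12-month record.

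This matters here for two reasons. The dropout allowance is large. Contact also differs between the arms: 18 supervised sessions over the year in one, and in the other no feedback or support contact apart from the 4-month assessment. Dropout that relates to early activity differently in the two arms is therefore plausible, though nothing in the documents shows that it will occur. At stake are some precision and some protection against bias for the two outcomes that took the sample from 180 to 312.

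**Working it through.** **1. Reproduce the stated power with the two-point model.** Inputs from Sample size calculation: 156 per group, 40% dropout, correlation 0.50, alpha 0.025 (taken as two-sided), standardized effects 0.45 and 0.40. With a constrained baseline and two visits, the 12-month effect equals ANCOVA in those observed at 12 months.

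- Observed per arm: 156 × 0.6 = 93.6
- Residual SD: √(1 − 0.50²) = 0.866
- Standard error: 0.866 × √(2/93.6) = 0.1266
- Effect 0.45: Φ(0.45/0.1266 − 2.241) = 90.5%
- Effect 0.40: Φ(0.40/0.1266 − 2.241) = 82.1%

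These match the stated figures of more than 90% and more than 80%. A t-based calculation gives 90.1% and 81.5%.

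**2. Precision gained from month 4.** The documents do not give the correlation r between 4 and 12 months or the fraction d lost by month 4. I assume r = 0.6 to 0.8, a baseline-to-4-month correlation of 0.5, and d = 10% to 40%. The partial correlation of months 4 and 12 given baseline is p = (r − 0.25)/0.75. With monotone dropout the variance ratio, three-point to two-point, is (1 − p²) + p² × 0.6/(1 − d).

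| r | p² | d = 10% | d = 20% | d = 30% | d = 40% |
|---|---|---|---|---|---|
| 0.6 | 0.218 | 0.927 | 0.946 | 0.969 | 1.000 |
| 0.7 | 0.360 | 0.880 | 0.910 | 0.949 | 1.000 |
| 0.8 | 0.538 | 0.821 | 0.866 | 0.923 | 1.000 |

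The reduction runs from 0% to 18%. At r = 0.7 and d = 20%, the ratio is 0.64 + 0.36 × 0.75 = 0.910, and the standard error becomes 0.1266 × √0.910 = 0.1208. Power rises from 82.1% to 85.8% at 0.40 SD (t-based: 81.5% to 85.3%) and from 90.5% to 93.1% at 0.45 SD. This equals 312/0.910 ≈ 343 patients under the two-point model. If all dropout precedes month 4 there is no gain.

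**3. Bias.** Simulation with 1,000,000 per arm, a true effect of 0.40 SD at 4 and 12 months, random loss of 10% or 20% by month 4, and 60% observed at 12 months in each arm. Dropout after month 4 is logistic in the 4-month value in one arm and random in the other. Absolute error of the two-point estimate, in SD:

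| r | 10% lost, log-odds 0.5 | 10% lost, log-odds 1.0 | 20% lost, log-odds 0.5 | 20% lost, log-odds 1.0 |
|---|---|---|---|---|
| 0.6 | 0.06 | 0.10 | 0.04 | 0.08 |
| 0.7 | 0.07 | 0.13 | 0.05 | 0.10 |
| 0.8 | 0.09 | 0.16 | 0.07 | 0.12 |

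The sign depends on which arm has the dependence. The three-point estimate is within 0.003 SD of the truth throughout.

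Two further cases limit the claim:

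- **Same dependence in both arms (log-odds 1.0), equal completion:** both models have an error of about 0.
- **Dropout in one arm driven by the 12-month value itself (log-odds 1.0):** the two-point error is 0.16 to 0.21 SD and the three-point error 0.08 to 0.17 SD. At r = 0.7 with 10% lost early the errors are 0.21 and 0.14. The bias shrinks but remains.

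**The case against.** The strongest reply is that the plan contains no error here. A two-point constrained model is valid and prespecified, and is unbiased if missingness depends only on baseline and arm. It also fits the objectives, which ask for steps and MVPA at one and two years but not at 4 months. The power statement is met as it stands. The likely precision gain is small, and any bias requires dropout that works differently in the two arms. Sensitivity analyses for missing data may sit in a statistical analysis plan that is not shown.

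Most of this stands, and it sets the weight of the point. It does not justify the restriction. The objectives explain why month 4 is not tested, but not why it is left out as a dependent variable. Including it adds no hypothesis. The restriction is also stated outright, so it is not a detail left for another document.

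A reader might infer several stronger things that the documents do not support:

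- **That the key secondary outcomes are underpowered.** Step 1 shows they are not.
- **That three time points remove dropout bias.** They do so only when dropout depends on values that were observed.
- **That 40% dropout is planned.** It is an assumed high value.
- **That the 4-month data are already in hand.** They are scheduled, and the article describes a trial still recruiting.
- **That month 4 is the best predictor of dropout or of 12-month activity.** No figure in the article bears on this.

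**Conclusion.** The point holds as a no-cost improvement. The plan leaves a scheduled measurement out of the model for its two key secondary outcomes, uses the corresponding measurement for the primary outcome, and gives no reason. The omission makes the missing-at-random assumption rest on baseline alone.

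The precision effect is modest: 0% to 18% of the variance, about 9% in the central case, over assumed correlations and early loss that the documents do not give. The bias effect is conditional. At 0.04 to 0.16 SD, set against target effects of 0.40 to 0.45 SD, it would matter, but it requires arm-specific dropout related to 4-month activity. The sample size and stated power are unaffected.

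**What to change.** In Statistical analysis, delete the parenthesis that limits the key secondary model to two visits. Analyse daily steps and MVPA with the model specified for pVO2: baseline, 4-month and 12-month values as dependent variables, unstructured covariance, and HFpEF stage as a factor. State that the 12-month contrast is the only tested estimate for each outcome, under the existing Bonferroni-Holm correction. The two-point model can be kept as a sensitivity analysis.

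The cost is one line of wording, with no new visit, measurement or test. The change should be made before any unblinded look at the data, so that it cannot appear to be data-driven.

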#### Health economic evaluation

*The health economic evaluation* will evaluate health outcomes [expressed as quality-adjusted life years (QALY)] and costs of the PRIORITY intervention compared to usual care. A cost-utility analysis will be performed applying a decision-analytic Markov model to predict costs and health effects of the intervention vs. usual care. A lifetime time horizon will be considered. The analysis will be conducted from a societal perspective, meaning that both direct and indirect costs will be included. Direct costs will include direct medical costs (e.g., hospitalization, nursing care, medication) and direct non-medical costs (e.g., travel costs). Indirect costs are those related to lost human productivity (for example productivity losses due to morbidity or mortality). The cost of delivering the program will be collected alongside the RCT. Information on participants’ health care resource use and absence from work will be obtained by a researcher using a questionnaire at T0, T1, T2 and T3 as shown in Table 3. Subsequently, resource use unit costs will be attached to the above mentioned data using publicly available databases (47). The ratio of the incremental costs to the incremental health effects, i.e., the incremental cost-effectiveness ratio (ICER) will be calculated. The model will link changes in exercise capacity and cardiovascular risk profiles to recurrent cardiovascular events and CVD mortality to estimate the cost-per-QALY associated with the PRIORITY intervention compared to usual care (48). One-way sensitivity and probabilistic sensitivity analyses will be performed to address the uncertainty related to key input parameters of the Markov model. In the one-way sensitivity analysis, the impact of key input parameters (e.g., costs, transition probabilities) on the ICER will be examined by varying their values separately. A probabilistic sensitivity analysis, based on 5,000 iterations, will be performed to evaluate the uncertainty for key input parameters by varying them concurrently.

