## Aims and objectives

The PRIORITY trial will evaluate the feasibility, clinical and cost-effectiveness of a hybrid (centre and home-based) personalized exercise and physical activity intervention to prevent the deleterious effects of sedentary ageing on the heart and forestall the development and progression towards overt HFpEF.

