### Eligibility criteria and recruitment

The trial population will comprise 312 men and women (aged ≥30 years) along the continuum of HFpEF who are on optimal medical treatment and stable regarding symptoms and pharmacotherapy for at least 4 weeks before enrolment in the trial. All patients should have internet access at home. To represent the distribution of HFpEF stage A–C in the population, this will include 150 patients with HFpEF stage A, 90 patients with HFpEF stage B and 72 patients with HFpEF stage C. Participants will be recruited during a 2-year period which started in September 2021. Local investigators at each participating site will assess patient eligibility. A detailed description of the inclusion and exclusion criteria is shown in Table 1. Potentially eligible patients will then be contacted by a member of the research team and provided with a full oral explanation of the design and purpose of the trial, responsibilities of the participants, reasonably foreseeable inconveniences, and confidentiality of the information collected.

**Table 1 T1:** Inclusion and exclusion criteria for the PRIORITY trial.

HFpEF stage	Inclusion criteria	Exclusion criteria

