## Conclusion

The PRIORITY trial aims to bridge the gap between guideline recommendations and the implementation into clinical practice by evaluating the effectiveness of a hybrid strategy for delivering personalized exercise therapy to the rapidly expanding population of patients with HFpEF stage A–C. The PRIORITY trial aims to provide the scientific evidence to support the use of remotely guided exercise therapy as an imperative preventive cost-effective treatment in the HFpEF continuum. The trial will focus on the prevention of progression of asymptomatic diastolic dysfunction towards symptomatic HFpEF (=primary prevention) and delaying progression of symptomatic HFpEF (=secondary prevention). This document provides a detailed description of the design, methodology and protocol of the PRIORITY trial. If the results of this trial are positive, this strategy of implementation of personalized exercise therapy can be easily extended to other patient populations with chronic diseases for whom exercise, and the adoption of a physically active heart healthy lifestyle are a core component in their disease management.

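### The cost-utility model names recurrent events as its only non-fatal cardiovascular outcome, which does not fit a trial that is 77% asymptomatic stage A/B and aims to prevent overt HFpEF

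*Protocol article*

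**What the plan says.** The Health economic evaluation section of the protocol article plans a cost-utility analysis "applying a decision-analytic Markov model to predict costs and health effects of the intervention vs. usual care", and adds: "A lifetime time horizon will be considered". One sentence says through which outcomes the treatment effect passes into QALYs: "The model will link changes in exercise capacity and cardiovascular risk profiles to recurrent cardiovascular events and CVD mortality". No other sentence in the article names the modelled outcomes, and the health states and transitions are not listed.

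The population is fixed under Eligibility criteria and recruitment: "this will include 150 patients with HFpEF stage A, 90 patients with HFpEF stage B and 72 patients with HFpEF stage C". Under Randomization and concealed allocation, stages A and B are both defined as asymptomatic, on the basis of risk factors without (A) or with (B) echocardiographic abnormality.

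The purpose is given under Aims and objectives, where the intervention is meant to "forestall the development and progression towards overt HFpEF". The Conclusion gives as a focus of the trial the "prevention of progression of asymptomatic diastolic dysfunction towards symptomatic HFpEF (=primary prevention". The Background names the same gap in evidence: cost-effectiveness in preventing overt HFpEF.

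**The concern.** A recurrent event presupposes an earlier one. The word is a deliberate qualifier, since leaving it out would have covered first and later events alike. Applied as written, it restricts the non-fatal side of the model to patients who already have an event behind them, although the economic question is largely one of primary prevention.

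Cost-effectiveness is a listed secondary objective, and the Discussion expects the result to inform reimbursement. Programme costs arise at every stage in the intervention arm. If non-fatal first events and the step to symptomatic disease carry no modelled consequence, avoiding them brings no long-term gain in the calculation, and a main part of the hoped-for benefit is not evaluated.

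**Working it through.** **1. Stage mix (Eligibility criteria and recruitment).**
- Plan's own total: 150 + 90 + 72 = 312, which agrees with the stated sample size.
- Stages A and B: 150 + 90 = 240, and 240/312 = 76.9%.
- Stage C: 72/312 = 23.1%.

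**2. Is an earlier event part of any stage definition?**
- Stage A: risk factors, no symptoms, no echocardiographic abnormality. No earlier event required.
- Stage B: risk factors, echocardiographic abnormality, no symptoms. No earlier event required.
- Stage C: Table 1 accepts a heart-failure hospitalisation, but also diuretic treatment, or symptoms or signs with an HFA-PEFF score of at least 5. An earlier hospitalisation is one route among several.

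So the named event class does not follow from the entry criteria of any stage, and it fits stages A and B least.

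**3. Outcomes the trial aims to prevent, set against those the sentence names.**

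| Outcome after randomisation | Named in the modelling sentence? |
|---|---|
| Death from cardiovascular disease, first event or not | Yes |
| Repeat non-fatal event in a patient with an earlier one | Yes |
| First non-fatal event, such as a first heart-failure admission | No |
| Progression from stage A or B to symptomatic HFpEF | No |

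The last two rows are those to which Aims and objectives and the Conclusion point.

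**4. Can other parts of the plan make up the difference?**
- EQ-5D-5L utilities feed the evaluation (health-related quality of life paragraph), and Table 3 schedules them at all four visits. Resource use and absence from work are collected at the same visits. A first admission or worsening within two years can therefore show in the trial data.
- Beyond two years the lifetime result rests on the model's links and transitions.
- The one-way and probabilistic sensitivity analyses vary input parameters of the model. They cannot bring back an event type that has no parameter.

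**5. Can the size be computed?** No. It would need event rates, transition probabilities, utilities and unit costs, and the article gives none. As an illustration under assumed annual non-fatal event rates r1 in stages A/B and r2 in stage C, the share of events arising in A/B is 240·r1 / (240·r1 + 72·r2):
- r1 = 1%, r2 = 15%: 2.4/(2.4 + 10.8) = 18%
- r1 = 2%, r2 = 10%: 4.8/(4.8 + 7.2) = 40%
- r1 = 3%, r2 = 5%: 7.2/(7.2 + 3.6) = 67%

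The answer is set by the assumed rates. The formula also treats every A/B event as a first one and every stage C event as a repeat, which step 2 does not support. It shows only that the article leaves the size open.

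**The case against.** The strongest reply is that this builds much on one adjective in a condensed account. The article does not say that first events or progression are excluded. It speaks of transition probabilities without saying which, cites a source for the modelling approach, and may leave the state structure to a health-economic plan. That stands as far as missing detail goes: the absence of a list of states is no fault in an article. It does not dispose of the point, because the sentence names a particular event class, and that class does not fit the trial. If a fuller plan models more, this sentence misdescribes it and still needs correcting.

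Four further objections limit the point, and all stand:
- Cardiovascular death is in the same sentence, so fatal first events are covered. A reader might infer that the model counts recurrent events and nothing else; the sentence itself rules that out.
- A reader might infer that first events and progression drop out of the QALYs and the cost-effectiveness ratio altogether. The two-year utility and resource-use data are not limited to stage C or to repeat events, so the possible loss lies in the extrapolation.
- Being free of heart-failure symptoms does not prove the absence of an earlier cardiovascular event. Table 1 neither requires nor generally excludes one. The 76.9% is the share with no earlier event required, not the share known to have had none.
- Prescribing a full stage-based model would be a modelling preference, not the correction of an error.

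**Conclusion.** The concern holds in a limited form. The event class stated for the lifetime model does not match a population in which 240 of 312 patients (76.9%) are asymptomatic with no earlier event required, nor the aim of preventing the development of overt HFpEF. Built as written, the model would extrapolate no gain from averted first non-fatal events or averted progression to symptomatic disease.

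If the intervention reduces these outcomes, its benefit would be expected to be understated. That rests on two assumptions: that the sentence is applied literally, and that the intervention does affect them. A reader might go on to claim a quantified upward bias in the cost-effectiveness ratio. The article does not support that, since no rates, utilities or costs are given from which to derive it. The point concerns a secondary objective and leaves the primary and key secondary analyses untouched.

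**What to change.** In the Health economic evaluation section, replace the outcomes now named in the modelling sentence with: *first and recurrent cardiovascular events (including heart-failure hospitalisation), progression to symptomatic HFpEF, and CVD mortality*. Include the added transition probabilities in the one-way and probabilistic sensitivity analyses already planned. The detailed state structure can stay in the health-economic plan.

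The cost is a change of wording plus more literature-based model inputs, with somewhat wider probabilistic uncertainty. No further patients or trial measurements are needed.
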